### Data collection and outcomes

The study evaluates the impact of statin prescription on two primary outcomes:

*HRQoL*, measured by the Patient-Reported Outcomes Measurement Information System 10-Question Short Form (PROMIS-10), which includes subscales for mental health and physical health.^39 40^*Three-point MACE-free survival*, defined as survival without any of the following MACEs: cardiovascular death, non-fatal myocardial infarction or non-fatal stroke. MACE events are self-reported by participants or reported by a proxy using a calendar returned every 3 months and are verified annually with treating physicians.

Secondary outcomes include functional outcome assessed using the modified Rankin Scale^41^; falling using a falls calendar; cognitive functioning using the Montreal Cognitive Assessment (MoCA)^42^ or the Telephone version of MoCA^43^; quality-adjusted life-years (QALYs) based on the EuroQol 5-Dimension 5-Level (EQ-5D-5L)^44^ questionnaire; and societal costs using The Older Persons and Informal Caregivers Survey–Minimum DataSet (TOPICS-MDS).^45^

At baseline, demographics, medication use and recent clinical metrics and laboratory values are extracted from the electronic patient record by local investigators. Furthermore, the PROMIS-10, MoCA, EQ-5D-5L, TOPICS-MDS and CFS are assessed. Follow-up continues for 24 months, with an optional 1-year extension for early enrollees. Assessment frequencies vary by outcome measure (figure 1). Participants, caregivers and local investigators are not blinded. However, all follow-up is conducted by investigators from the central research team who are blinded to treatment allocation.

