### Sample size

We hypothesise that in frail older patients with recent ischaemic stroke or TIA, starting statins will cause a clinically relevant decrease in HRQoL without substantially improving MACE-free survival. For HRQoL, we expect baseline PROMIS-10 subscale scores of approximately 45, with an SD of 9.0 and a Minimal Clinically Important Difference of 4.5, approximated as 0.5 SD.^46 47^ Frailty and prior ischaemic stroke or TIA both reduce life expectancy in older adults.^11^,^13^ Based on previous studies, we estimate a 2-year survival rate of 52% in the control group.^48^,^50^ Cardiovascular events increase with age, and this older, frail cohort is therefore at higher baseline risk for MACE. Statin use in secondary prevention after ischaemic stroke or TIA in people of all ages has shown reductions in recurrent stroke (HR 0.89), myocardial infarction (HR 0.55) and cardiovascular death (HR 0.78).^51^ For our composite outcome of MACE-free survival in frail older patients, higher baseline risk and limited life expectancy support an HR estimate of 0.70. A total of 612 participants provide 99% power to detect a >4.5-point decrease in HRQoL and 80% power to detect an HR of 0.70 for MACE-free survival, using a two-sided alpha of 0.05, and accounting for 5% loss to follow-up.^52^ Loss to follow-up is expected to be minimal, as most discontinuations will involve study outcomes (MACE or non-cardiovascular death), and partial follow-up still contributes to the time-to-event analysis.

Sample size calculations are based on the Hotelling Lawley Trace test, using a linear exponent autoregressive model with a base correlation of 0.5 and a decay of 0.3.^53^ With approximately 6800 eligible patients annually in the Netherlands based on Dutch health insurance data,^54^ we expect to reach our recruitment target.

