#### Primary outcomes

HRQoL (PROMIS-10) will be analysed using a mixed model for repeated measures, with deceased patients scored as 0. Group differences over time will be reported with two-sided 95% CIs. MACE-free survival will be analysed using a time-to-event approach, with patients who withdraw early being censored at the time of withdrawal. The effect of statins will be expressed as an HR using a Cox regression model. Adjustments will be made for the type of event (TIA or ischaemic stroke), as these conditions may differ in baseline risk and prognosis. The assumption of proportionality will be tested, and Kaplan-Meier curves will visualise group differences in survival. Exploratory subgroup analyses of the primary outcomes will be performed by age, sex, type of event (ischaemic stroke or TIA), degree of frailty and LDL value.

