#### Secondary outcomes

Functional outcome and cognitive functioning will also be analysed using a mixed model for repeated measures. Falls will be assessed with a time-to-event analysis and Kaplan-Meier curves for fall-free survival. Total falls per participant over 2 years will be analysed using a binomial negative regression analysis. Bivariate regression analyses will estimate cost and effect differences. Incremental cost-effectiveness ratios (ICERs) will be calculated by dividing the difference in the mean total costs between the treatment groups by the difference in mean effects on the primary outcomes and QALYs.^55^ Statistical uncertainty surrounding the ICERs will be evaluated using bias-corrected and accelerated bootstrapping with 5000 replications, and presented via cost-effectiveness planes and cost-effectiveness acceptability curves.^56^

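### Non-cardiovascular death is left out of the MACE-free survival definition but seems to be counted in its sample size, and Kaplan-Meier curves that censor it would overstate MACE risk

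*Protocol article*

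**What the plan says.** All references are to the Protocol article.

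- **Data collection and outcomes**: the second primary outcome, three-point MACE-free survival, is "defined as survival without any of the following MACEs: cardiovascular death, non-fatal myocardial infarction or non-fatal stroke". Non-cardiovascular death is not listed.
- **Sample size**: expected loss to follow-up is small because "most discontinuations will involve study outcomes (MACE or non-cardiovascular death". The only event-rate input is "we estimate a 2-year survival rate of 52% in the control group". The claim for this outcome is "80% power to detect an HR of 0.70 for MACE-free survival, using a two-sided alpha of 0.05", with 612 participants and 5% loss to follow-up.
- **Primary outcomes** (Statistical methods): the effect measure is a Cox HR, withdrawal is the only stated reason for censoring, and "Kaplan-Meier curves will visualise group differences in survival". The only rule for death is a PROMIS-10 score of 0.
- **Secondary outcomes**: "Falls will be assessed with a time-to-event analysis and Kaplan-Meier curves for fall-free survival", and "Total falls per participant over 2 years will be analysed using a binomial negative regression analysis". No rule for death is given.

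**The concern.** A reader cannot tell whether a non-cardiovascular death is a primary event, a censoring or a competing event. The endpoint definition implies it is not an event. The Sample size section groups it with the outcomes and uses an input worded as overall survival. In a frail population aged 70 or over this is not a marginal category.

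Two things depend on the answer. The first is the number of primary events, and so the stated 80% power. The hypothesis expects no substantial improvement in MACE-free survival, so a null result from an underpowered comparison could be taken as confirmation. The second is the absolute risk shown by the curves. If non-cardiovascular deaths are censored, Kaplan-Meier treats the dead as if they could still have a MACE, and one minus the curve exceeds the real 2-year risk.

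**Working it through.** **1. Reproducing 612.** Inputs from the article: HR 0.70, two-sided alpha 0.05, power 80%, 1:1 allocation, control 2-year survival 52%, 5% loss.

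- Schoenfeld events: 4(1.96 + 0.8416)² / (ln 0.70)² = 247.
- Control failures: 1 − 0.52 = 0.480. Statin failures: 1 − 0.52^0.70 = 0.367. Mean: 0.4236.
- 247 / 0.4236 = 584, and 584 / 0.95 = 615, within 1% of 612.
- In reverse: 612 × 0.95 = 581.4, and 581.4 × 0.4236 = 246 events, giving 79.9% power.

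Freedman's formula gives 253 events and N = 630, within 3%. One-sided versions give 485 to 495 and do not fit. The stated inputs therefore yield 612 when every one of the 48% control failures is a primary event with HR 0.70.

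**2. Power if only some failures meet the definition.** The article gives no split, so the share s is an assumption. Constant hazards are assumed, with cumulative 2-year hazard H = −ln 0.52 = 0.654. MACE takes m = sH and non-cardiovascular death takes k = (1 − s)H. HR is 0.70 on MACE and 1 on non-cardiovascular death. Cumulative incidence of MACE is m/(m + k) × [1 − exp(−(m + k))], with 0.70m replacing m in the statin arm. Events = 581.4 × the mean of the two arms.

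| MACE share s | MACE events | Power, MACE only | N for 80% | HR if any death counts | Power, any death |
|---|---|---|---|---|---|
| 100% | 246 | 80% | 614 | 0.70 | 80% |
| 80% | 196 | 70% | 774 | 0.76 | 59% |
| 50% | 121 | 50% | 1252 | 0.85 | 26% |
| 30% | 72 | 33% | 2102 | 0.91 | 12% |

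The diluted HR is 0.70s + (1 − s).

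If 52% is overall survival, non-fatal MI and stroke come on top of the deaths. With an assumed 30% to 70% of deaths cardiovascular and a 2-year non-fatal MACE risk of 10% to 20%, MACE-only power runs from 45% to 78%.

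**3. Kaplan-Meier against cumulative incidence, control arm at 2 years.** One minus Kaplan-Meier with other deaths censored is 1 − exp(−m).

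| Assumption | 1 − KM | Cumulative incidence | Gap (points) |
|---|---|---|---|
| s = 80% | 40.7% | 38.4% | 2.3 |
| s = 50% | 27.9% | 24.0% | 3.9 |
| s = 30% | 17.8% | 14.4% | 3.4 |
| 40% of deaths CV, plus non-fatal MACE at 0.10/year | 37.0% | 31.0% | 6.0 |
| 50% of deaths CV, plus non-fatal MACE at 0.10/year | 41.0% | 35.4% | 5.6 |

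For the last two rows the all-cause hazard is 0.654 / 2 = 0.327 per year. With a 40% share, the MACE hazard is 0.4 × 0.327 + 0.10 = 0.231 and the other hazard is 0.196.

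The difference between arms is distorted less. At s = 50% it is 27.9 − 20.5 = 7.4 points by Kaplan-Meier and 24.0 − 17.6 = 6.4 by cumulative incidence. The subdistribution HR across these shares is about 0.70, close to the cause-specific value.

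**4. Falls (secondary).** This step takes 52% as overall survival. Control mean time alive over 2 years is 0.48 / 0.327 = 1.47 years. With HR 0.70 on cardiovascular deaths only, assumed to be 40% to 50% of deaths, the all-cause HR is 0.88 to 0.85. Mean time is then 1.52 to 1.53 years, a ratio of 1.036 to 1.045. With HR 0.70 on all deaths it is 1.605 / 1.468 = 1.09.

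**The case against.** - **The Cox model is sound.** A reader might infer that the HR is biased because non-cardiovascular death is ignored. It is not: with those deaths censored, Cox estimates the cause-specific HR. This part of the objection stands in full.
- **The curves are only for display.** The plan derives no 2-year risk from them. If any death counted as failure, Kaplan-Meier would be correct. A reader might also infer that inflated risks enter the cost-effectiveness ratios, but the Secondary outcomes section names no Kaplan-Meier estimate. Both points limit the harm. Still, under the definition as written, the curves are the only named display of absolute MACE risk, and it would be too high.
- **The Sample size sentence is about loss to follow-up.** Death is an outcome of a kind, since it scores 0 on PROMIS-10. The sentence alone could be loose wording. The 52% input is harder to set aside, because it drives the event count.
- **The 52% may mean MACE-free survival.** The arithmetic fits that. The 80% would then stand, the term used for the input would be wrong, and expected mortality would not be stated. The status of non-cardiovascular death would still need settling.
- **Falls are analysis-plan detail.** An offset is commonly left to the SAP, which is not shown, and fall-free survival may count death as an event. This stands, so the falls point is only a suggestion.

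**Conclusion.** The point holds for the primary outcome. The endpoint definition and the Sample size section do not agree on non-cardiovascular death, and the analysis section does not settle it. The stated 80% power rests on all 48% of control failures being primary events. With assumed MACE shares of 80%, 50% and 30%, it is about 70%, 50% and 33%. If non-fatal events are added to 48% mortality, it is 45% to 78%. Kaplan-Meier with non-cardiovascular deaths censored would overstate 2-year MACE risk by about 2 to 6 points. All these ranges rest on event splits that the article does not give and on constant hazards.

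Three stronger readings are not supported. The trial is not shown to be underpowered, because 52% may be MACE-free survival. It is also not shown that about half of participants would die of competing causes. The 48% is a control-arm, all-cause figure, and with 40% to 50% of deaths cardiovascular, non-cardiovascular deaths would be 0.48 × 0.5 to 0.48 × 0.6, or 24% to 29% of controls. Nor is a 9% artefact in falls the expected size: it needs HR 0.70 on all deaths, and roughly 4% follows if only cardiovascular deaths are affected.

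**What to change.** 1. Keep the three-point definition, declare non-cardiovascular death a competing event, and align the Sample size and Primary outcomes sections with it.
2. Keep the Cox model and label its result the cause-specific HR. Replace the Kaplan-Meier curves with Aalen-Johansen cumulative incidence and report the 2-year risk difference with its 95% CI.
3. Report MACE or any death as a named supportive endpoint, for which Kaplan-Meier is appropriate.
4. State whether 52% is overall or MACE-free survival, give the expected split of events, and restate the power for the chosen definition.
5. As a minor addition, use log person-time alive and in follow-up as the offset in the fall-count model.

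Items 1 to 3 and 5 cost wording and a few lines of code. They need no new data, since the definition already requires cardiovascular deaths to be told apart from others. Item 4 costs a recalculation. If the power proves materially lower, the sponsor must decide whether to change the sample size or the claim. Recruitment is planned to January 2027 and data collection to January 2029, which leaves time to settle this before analysis.

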#### Secondary outcomes

Functional outcome and cognitive functioning will also be analysed using a mixed model for repeated measures. Falls will be assessed with a time-to-event analysis and Kaplan-Meier curves for fall-free survival. Total falls per participant over 2 years will be analysed using a binomial negative regression analysis. Bivariate regression analyses will estimate cost and effect differences. Incremental cost-effectiveness ratios (ICERs) will be calculated by dividing the difference in the mean total costs between the treatment groups by the difference in mean effects on the primary outcomes and QALYs.^55^ Statistical uncertainty surrounding the ICERs will be evaluated using bias-corrected and accelerated bootstrapping with 5000 replications, and presented via cost-effectiveness planes and cost-effectiveness acceptability curves.^56^

## Ethics and dissemination

The protocol was registered on ClinicalTrials.gov (NCT06785727) on 19 December 2025. The study complies with the Declaration of Helsinki and is classified as a healthcare evaluation, comparing two standard-of-care strategies recommended in Dutch guidelines. Given the study’s low-risk nature, a Data Safety Monitoring Board and subject insurance were not required. All centres are covered by institutional liability insurance in accordance with the Dutch Medical Research Involving Human Subjects Act. Adverse events are recorded in Castor; serious adverse events are reported to the central research team and included in annual safety reporting.

Recruitment began in March 2025; the last patient is expected to be included in January 2027, with data collection concluding by January 2029. Data are handled in accordance with the General Data Protection Regulation (European Union) 2016/679. Independent monitoring is performed by the Amsterdam UMC Clinical Monitoring Center, following the study’s monitoring plan (online supplemental appendix 3: monitoring plan). Baseline data are extracted from hospital records and questionnaires; follow-up data come from general practitioners and participant questionnaires. Source documents are securely stored at study sites, while follow-up data are centrally managed at Amsterdam UMC. All study data will be archived for 25 years. Deidentified data will be made available on reasonable request, in line with ethical approvals and data protection regulations. Further details on data management, storage and governance are available in online supplemental appendix 4: data management plan.

The results of this trial will be submitted for publication in peer-reviewed open access journals and presented at national and international conferences. In collaboration with the Dutch Brain Injury Association, findings will also be disseminated through patient networks and the association’s website to reach a broader public. This study will provide valuable insights and have direct implications for clinical practice. Results will be integrated into Dutch national guidelines, facilitating implementation in routine care.

## Discussion

The SAFEST-RCT evaluates the effectiveness of starting statin therapy after ischaemic stroke or TIA in frail older adults, a population typically excluded from trials.^8^ With no clear guidelines for this population,^32 33^ statin prescribing varies widely in this group. This trial aims to reduce such variability by providing clear clinical guidance.

Due to a lack of clear guidelines on statin discontinuation, management practices also vary for patients already on statins at the time of their event.^32 33^ Initially, we intended to study both initiation and discontinuation of statins within one RCT. However, ethical concerns prevented randomisation for discontinuation. As a result, we are now conducting ‘SAFEST—the prospective cohort study’ alongside the SAFEST-RCT. This observational study investigates continuing versus discontinuing statins in frail older adults already on statin therapy at the time of their ischaemic stroke or TIA. Data from this cohort will be used to emulate a trial estimating the effects of discontinuing.^57^

Our study has several strengths. Its randomised design minimises selection bias, and the multicentre inclusion of 22 academic and general hospitals across the Netherlands enhances representativeness of the national population. This includes individuals with a migration background, provided they are proficient in Dutch or supported by a proxy. The use of the validated CFS to assess frailty strengthens the study’s methodology.^35^ Given the international use of the CFS and the comparability of Dutch healthcare to other high-income countries, findings are likely generalisable beyond the Netherlands.^58^ To our knowledge, no other trials are currently investigating the effect of statins following an ischaemic stroke or TIA in frail older adults.

This study has several limitations. First, its open-label design may introduce bias, as patients’ awareness of their treatment allocation could influence the perceived benefits, adverse effects and responses to the patient-reported PROMIS-10 questionnaire, which is the primary outcome in this study. This design was chosen to minimise patient burden by avoiding placebo use and to prevent confusion in medication management, which is particularly important in frail older adults. The direction and magnitude of this potential bias are uncertain; participants’ beliefs about their treatment may affect questionnaire responses either positively or negatively. To minimise bias, outcome assessments are conducted by study team members who remain blinded to treatment allocation. Second, the exclusion of individuals unable to provide informed consent, such as those with severe cognitive impairment or disabling aphasia, may limit the generalisability of findings to the most severely affected populations. Third, the exclusion of patients unable to communicate in Dutch may introduce bias, as non-Dutch-speaking residents could have a different profile of stroke risk factors and comorbidities. To minimise this risk, patients with limited Dutch proficiency are allowed to participate with support from a proxy. Fourth, adherence to statin therapy will be assessed through pharmacy dispensing records, which reflect prescription collection but not actual medication intake. This approach was chosen to minimise participant burden in this frail population, in which more direct methods, such as blood tests, pill counts or adherence questionnaires, as described in the review of López-Pineda *et al*,^59^ were not feasible. Fifth, in the intervention group, the choice of statin type and dose is left to the treating neurologist according to routine care and the Dutch Stroke guideline, which may introduce some heterogeneity in treatment. Lastly, the study focuses solely on statin therapy and does not consider other lipid-lowering agents such as ezetimibe, bempedoic acid or proprotein convertase subtilisin/kexin type 9 inhibitors, which may be explored in future research.

In summary, the SAFEST-RCT and its complementary cohort study aim to fill a critical evidence gap in the management of statin therapy in frail older adults after ischaemic stroke or TIA, to provide essential guidance for clinical decision-making in this vulnerable and understudied population.
